143 NicaPlant® up to patient discharge, or day 21, whichever occurs first.

144 Clinical Outcomes will be recorded at 12 weeks and 1 year (week 52) after the aSAH.

145 A data safety monitoring board (DSMB) will be set-up to monitor safety throughout the trial  
146 period and provide recommendations for any necessary actions. A steering committee will  
147 receive and review the reports from the DSMB and take action as appropriate.

The final analysis will be carried out when the final patient completes the week 12 assessment. Data collected for patients at Week 52 after aSAH will be analysed and included as an addendum to the final report.

Given that NicaPlant® is implanted at the time of aneurysmal clipping, it should be emphasised that the investigational product cannot be withdrawn after implantation.

In summary, published data on the safety and effectiveness of NPRIs supports the premise that NicaPlant® offers significant potential therapeutic benefits, without significant clinical risk.

Furthermore, the results of the phase IIa study involving a total of 10 actively treated patients (with 2 patients each in 3 and 6 Implant groups and 3 patients each in 10 and 13 Implant groups) demonstrate that NicaPlant® was safe and well-tolerated up to 13 implants/ patient.

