#### 248 ***Safety:***

#### 249 **Daily assessments:**

- 250 • Adverse events (AEs)
- 251 • Shunt-dependent hydrocephalus (to Day 21 $\pm$ 1 or patient discharge)
- 252 • Bacterial meningitis (to Day 21 $\pm$ 1 or patient discharge)
- 253 • Change in grading of AE severity

254

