#### 255 **At the defined visits 1 to 5:**

256

- 257 • Vital Signs: blood pressure, pulse rate, respiratory rate and body temperature

- 258 • Electrocardiogram (ECG)

- 259 • Full blood count, urea and electrolytes, liver function tests, C-reactive protein

260 Safety assessments will be made from baseline until discharge or day 21±1 and at all  
261 subsequent visits. Adverse Events occurring after day 21±1 will be collected but will no  
262 longer be considered treatment emergent.

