### **Inclusion criteria**

1. Austria: Informed consent is obtained from patients with capacity. If patients lack capacity, informed consent is obtained from a personal legal representative. If no suitable personal legal representative is available and the treatment needs to be given urgently, written informed consent will be obtained as soon as the participant is responsive or a representative is available.
- Germany: An independent physician is to be consulted to confirm that the presumed will of the patient on the participation in the study has been determined and respected. Written informed consent will be obtained as soon as the participant regains capacity.
2. Male or female patients aged 18 to 75 years (inclusive).
3. World Federation of Neurological Surgeons (WFNS) grade III-IV.
4. Ruptured saccular aneurysm, confirmed by angiography.
5. Onset of aSAH clinical symptoms within the preceding 48 hours.
6. Treatment of aneurysm via surgical clip ligation within 72 hours of aSAH is achievable.
7. Female patients of child-bearing potential must have a negative pregnancy test (urine or serum) at screening and must agree to use adequate birth control up to 12 weeks after implantation of the study drug. Female patients are considered to be not of child-bearing potential if they have a history of tubal ligation or hysterectomy or are post-menopausal with a minimum of 2 years without a natural menstrual cycle. Male

patients must agree to use adequate birth control up to 12 weeks after implantation of the study drug.

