## 586 **STUDY PLAN**

### 587 **Study Timings**

588 Timing in the study is measured from time of aneurysm rupture; as the time of rupture cannot  
589 be determined precisely it shall be defined as the time from onset of first symptoms.

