1031       AEs occurring after day 21±1 will be collected but will no longer be considered treatment  
1032       emergent.

1033       **Reporting serious adverse events to the sponsor**

1034       All SAEs must be reported to NeuroScios PV within 24 hours of awareness, regardless of  
1035       causal relationship. For SAE reporting, the part 11 CFR compliant safety database Aquila  
1036       CTPV provided by NeuroScios GmbH will be used. For each trial site investigators will be  
1037       provided with an access to the database on a dedicated server. SAEs will be signed  
1038       electronically by the investigator within the database and will be automatically distributed to  
1039       PV, sponsor representative(s), the project manager and the investigator as confirmation of  
1040       receipt. Sponsor medical monitor/medical advisor is responsible for expectedness evaluation  
1041       of the reported event.

1042       Each SAE form must be printed by a member of the PV team and retained in the TMF in  
1043       paper form. MedDRA coding of events will be performed by PV Unit within Aquila CTPV.

1044       All SAEs occurring until 30 days after study end of each patient must be reported to by the  
1045       Investigator or designated assistant is made aware of the event and by full report as soon as  
1046       possible thereafter.

1047       In case of system failure of Aquila, all SAEs must be completed in the corresponding paper  
1048       version in the investigator site file (ISF) and emailed to: [[contact]](mailto:[contact]) within  
1049       24 hours after knowledge of the event.

1050

1051       Pregnancies occurring during the study must be reported immediately by fax or email using  
1052       the Pregnancy Report Form.

1053       In case that an event is both serious and unexpected and a reasonable causal relationship to  
1054       IMP administration is given, it constitutes a suspected unexpected serious adverse reaction.  
1055       PV will report any SUSARs occurring in the trial to the relevant CAs, Ethics Committees  
1056       (EC(s)), all study PIs and the DSMB as outlined in section 0.

1057       NeuroScios will keep the Investigator and DSMB (section 0) informed of all SUSARs  
1058       reported to them for the product under investigation, from anywhere in the world, for the  
1059       duration of the trial at a frequency appropriate to the trial.

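### Two primary safety endpoints, hydrocephalus and meningitis, are counted only to discharge or day 21, so observation time depends on discharge, and the promised later safety checks are not in the visit lists

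*Protocol*

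**What the plan says.** Safety and tolerability of the ten-implant dose is one of the two primary objectives. Under Primary Outcome Endpoints, Safety, Daily assessments, the list includes "Shunt-dependent hydrocephalus (to Day 21"±1 or patient discharge, and bacterial meningitis with the same limit. The Risks / benefits text in the background describes the safety assessments as running "up to patient discharge, or day 21, whichever occurs first". Study Timings sets the clock: "Timing in the study is measured from time of aneurysm rupture". Clip ligation and implantation may follow up to 72 hours later (Visit 2).

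On the later period the protocol says several things:

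- Under the heading for visits 1 to 5: "Safety assessments will be made from baseline until discharge or day 21±1 and at all" subsequent visits.
- Continuous Assessment: adverse events, meningitis and hydrocephalus are assessed as they arise, with no end day.
- Recording adverse events: "AEs occurring after day 21±1 will be collected but will no longer be considered treatment" emergent.
- Reporting serious adverse events: serious events are reported until 30 days after each patient's study end.
- The Visit 6 (Week 12) and Visit 7 (Week 52) lists: mRS, GOSE, MoCA, EQ-5D-5L, SF36 and mortality due to SAH, and nothing else.

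**The concern.** Discharge happens after randomisation and can respond to treatment. An implant that prevents vasospasm may shorten stay, and one that causes complications may lengthen it. The protocol lists length of ICU and hospital stay among its exploratory outcomes and plans to compare them between arms. If counting stops at discharge, the two endpoints mix the rate of the event with the time the patient was watched. The arm that leaves hospital sooner would then look safer even if the underlying rates were equal.

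A second problem adds to this. After discharge, the scheduled visits contain no item asking about shunt surgery, infection or adverse events, although the safety section promises assessments at those visits. A shunt placed or an infection treated elsewhere could reach the database late or not at all. Safety will be summarised descriptively with 20 patients per arm, so each event moves an arm's rate by 1/20 = 5 percentage points, and a few uncounted events would change how the table reads.

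**Working it through.** The protocol gives no figure on this point. Its one calculation, 84% power for the vasospasm endpoint, does not bear on it. (It reproduces: exact enumeration of the two-sided Fisher test with 20 per arm, 20% against 70%, gives 84.6%.) The check is day arithmetic and a comparison of passages.

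**Inputs**

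- End of counting: the earlier of discharge (day D after rupture) and day 21±1 (Daily assessments; Risks / benefits).
- Clip ligation: C = 0 to 3 days after rupture (Visit 2, within 72 hours).
- Discharge before day 21 is foreseen: Visits 4 and 5 are both brought forward to discharge if that comes first. The protocol gives no distribution of discharge days, so the D values below are assumptions.

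**Observation time after clipping:** W = min(D, 21±1) − C

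- In hospital to the end, with the ±1 day: 20 − 3 = 17 to 22 − 0 = 22 days. At day 21 exactly: 18 to 21 days.
- Discharged on day 14: 14 − 3 = 11 to 14 − 0 = 14 days.
- Discharged on day 12: 12 − 3 = 9 to 12 − 0 = 12 days.

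**Ratio to a patient who stays to day 21, at the same C**

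- Day 14: 11/18 = 0.61 to 14/21 = 0.67.
- Day 12: 9/18 = 0.50 to 12/21 = 0.57.

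If events are infrequent and occur at a constant rate that is the same in both arms, expected counts are proportional to observation time. The ratios are then also ratios of expected events: a day-14 discharge gives 33% to 39% fewer, and a day-12 discharge 43% to 50% fewer. At arm level this deficit is multiplied by the difference between arms in the proportion leaving early. For day 14 the possible range runs from 0 (same discharge pattern in both arms) to 33–39% (all of one arm and none of the other). The documents do not say where in that range the trial would fall.

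**Passages side by side.** Take a CNS infection with a positive CSF culture on day 18. In a patient still in hospital it counts as the meningitis endpoint. In a patient discharged on day 12 it does not, although it precedes the day 21±1 cut-off and is a treatment-emergent adverse event. Now take a shunt needed in week 5 after a day-12 discharge. It is outside the hydrocephalus endpoint and is not treatment emergent, but it is an adverse event to be collected. If it leads to an unplanned overnight admission, it is also a serious one.

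**The schedule after discharge.** From day 21 to the Week 12 visit is 84 − 21 = 63 days; after a day-12 discharge it is 72 days. The safety section promises assessments at all later visits, and Continuous Assessment has no end day. The two later visit lists name no safety item apart from mortality due to SAH, and the endpoint list stops the two named events at discharge or day 21. These statements do not describe the same data collection.

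**The case against.** The strongest reply is that late events are not ignored. All adverse events during the study must be documented, including those after day 21±1. Serious events are reported regardless of causality until 30 days after study end. Data Descriptions covers Visits 1 to 6, and the final analysis follows Week 12. Safety Endpoints summarises all adverse events, with hydrocephalus and meningitis named separately, and is not restricted to treatment-emergent events. The Week 52 addendum is to report further adverse events, specifically CNS-related ones. All of this stands. It rules out saying that late harms disappear from the safety result, but it does not change the window of the two named endpoints or put a question on the later visit lists.

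It can also be said that the ICU team is blinded, so discharge should not be steered by knowledge of the arm. That is fair, but a real treatment effect on recovery would change length of stay without anyone being unblinded.

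Two stronger readings are tempting. First, a reader might infer a 12-week exposure period, because patients "must agree to use adequate birth control up to 12 weeks after" implantation. The documents do not support this. It is a contraception rule, and no passage says exposure lasts that long. Where the protocol deals with drug levels and drug effects it works with 21 days: phase IIa peak concentration over days 0 to 21, PK sampling to discharge or day 21, plasma parameters for days 1 to 21, and hypotension up to day 21. Second, a reader might extend the discharge limit to all treatment-emergent adverse events. That cut-off is day 21±1 for every patient and does not mention discharge, so the unequal-window argument does not apply to it.

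**Conclusion.** The point holds for the two named endpoints and for the late safety schedule. Hydrocephalus and meningitis are observed for a length of time that discharge decides. A discharge on day 12 or 14 gives 50% to 67% of the observation time of a patient who stays to day 21. Any bias between arms depends on how far their discharge patterns differ, which is unknown beforehand and may be nil. The percentages rest on assumed discharge days and a constant event rate.

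The day 21±1 treatment-emergent limit is not shown to be wrong; the protocol only gives no reason for it. Measuring from rupture shortens the period after clipping by at most 3 days in either arm and is a minor matter. The safety evaluation remains usable. This is an inexpensive correction to a primary endpoint definition, together with a conflict between sections that should be removed. The window is fixed in the protocol itself, so the point does not turn on what a statistical analysis plan might add.

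**What to change.** Reconcile the Risks / benefits text, the Daily assessments list, the paragraph under visits 1 to 5, Continuous Assessment and the Visit 6 and 7 lists, so that they state one safety period and one set of assessments.

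- Count shunt-dependent hydrocephalus and bacterial meningitis in both arms over the same fixed window from clip ligation, regardless of discharge. The existing Week 12 visit (81 to 84 days after clipping) is one workable end point; keep the day-21 count as an additional table.
- Add adverse event review, and shunt surgery and CNS infection since the last visit, to Visits 6 and 7.
- State the reason for the day 21±1 treatment-emergent cut-off, and tabulate later adverse events by arm.

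The cost is protocol wording and a few CRF questions at two visits that already take place. There is no extra visit or procedure. The small downside is that more background, disease-related late events will be listed in both arms; the concurrent control arm gives the comparison needed to read them.

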#### 1068 **Hospitalisation**

1069 The length of ICU stay and the length of hospital stay after aSAH will be recorded.

1070

#### 1071 **DATA MANAGEMENT**

1072 Data will be recorded on a CRF by the Investigator (or designee). The database, data entry  
1073 and electronic checks will be developed using a Clinical Database Management System.  
1074 Computerised data cleaning checks will be used in addition to manual review to check for  
1075 discrepancies and to ensure consistency and completeness of the data. An electronic audit  
1076 trail system will be used to track all data changes in the database.

1077 A 100 % quality control check of the data entry will be performed on a randomly selected  
1078 sample of the CRFs.

1079 Medical history findings and adverse events will be coded using the MedDRA dictionary;  
1080 medications will be coded using the World Health Organisation Drug dictionary.

1081 A detailed Data Management Plan will be produced before study commencement.

1082

#### 1083 **STATISTICAL ANALYSIS PLAN**

1084 A detailed statistical analysis plan (SAP) will be produced after finalising the protocol.

#### 1085 **Power & Sample size**

1086 In order to ensure that the investigation of efficacy is adequately powered, the sample size  
1087 requirements are derived for the primary endpoint of interest.

1088 The primary endpoint is the Incidence of Cerebral Angiographic Vasospasm (Moderate to  
1089 Severe) at day 8 and these rates are compared for the active and control treatment groups  
1090 using the Fishers Exact test for differences in proportions. PASS software (Version 12; NCSS  
1091 LLC, Kaysville, UT, USA) was used for all calculations.

1092 A total of 40 patients (20 in each group) is in fact sufficient to detect a clinically relevant  
1093 difference of 50% between the active treatment and control group (active: 20%, control:  
1094 70%) with a two tailed significance level of 5% and 84% power.

1095 The Incidence rates from previous published work (Barth et al.,2007) were used as an  
1096 indicator of the likely incidence rates observed in a similar population with similar  
1097 investigations (Active: 7%, Control: 73%).

## 1098 **Populations for analysis**

1099 Three main patient analysis sets will be described. These include the Full Analysis Set (FAS),  
1100 Per protocol (PP) and Safety sets. The FAS set is considered the primary analysis set for all  
1101 primary and secondary efficacy endpoints. The PP set will also be used to analyse the  
1102 primary efficacy endpoint and will consist of those patients in the FAS set without any major  
1103 protocol deviations. These will be defined in the SAP. The Safety set is considered the  
1104 primary set for all safety evaluations.  
1105 For the purpose of evaluating PK and PD endpoints, separate Pharmacokinetic and  
1106 Pharmacodynamic analysis sets will be defined.

1107 All available data of deceased patients will be included in the analysis sets.

1108

1109

## 1110 **Statistical endpoints**

### 1111 ***Aim:***

1112 The objective is to assess the efficacy of NicaPlant® (active group) in comparison to routine  
1113 Standard of care (control group). This will be based on statistical methods and be supported  
1114 by clinical assessment of the relevance of the overall findings.

### 1115 ***Null Hypothesis:***

1116 As this is an evaluation of the superiority of NicaPlant® over Standard of care. The Null  
1117 hypothesis assumed throughout that there is no difference between the active and control  
1118 groups for any of the assessments performed. The Alternative hypothesis is that the two  
1119 groups do in fact differ.

1120 A series of hypothesis tests and, where appropriate, supporting statistical models will be used  
1121 to investigate these differences. Where possible, indicators of statistical significance (p  
1122 values) will be quantified with estimates of the magnitude of the treatment differences and  
1123 supporting the 95% confidence intervals.

### 1124 ***Data Descriptions:***

1125 Data will be summarised according to patient population (FAS/PP/Safety), dose group (10  
1126 Implant/Control), assessment (Visit 1-6 / day where appropriate) and time (where  
1127 appropriate). Data collected on visit 7 will be reported and analysed in an addendum to the  
1128 study report.

1129 Categorical variables will be summarised as proportions (with 95% Clopper-Pearson  
1130 confidence intervals) and frequencies (if appropriate) and as odds ratios (with 95% Wald  
1131 confidence intervals), where logistic regression models are used. Continuous variables will be  
1132 summarised as Least square means and 95% confidence intervals, where analysis of variance

1133 (ANOVA) models are used and then also as supporting descriptive statistics (n, mean,  
1134 median, standard deviation, minimum, and maximum). Graphical displays appropriate to  
1135 these types of data will be used to present important findings.

1136 ***Treatment Group Comparability:***

1137 Surgical details (including Clip ligation & Implantation) and measures at baseline (including:  
1138 demographics, medical history, concomitant medication, physical examination, pregnancy  
1139 test) will be summarised descriptively by treatment group (10 Implant/Control) and overall.  
1140 No formal comparisons of the treatment groups at baseline will be made.

1141 ***Efficacy Endpoints:***

1142 The primary efficacy endpoint is the incidence of cerebral angiographic vasospasm (moderate  
1143 or severe) at Day 8±1. This is considered a binary outcome and the difference between the 10  
1144 Implant and Control groups will be investigated using Fishers Exact test. Proportions in the  
1145 two groups with 95% Clopper-Pearson confidence intervals will be used to quantify the  
1146 magnitude of the difference. In case cerebral vasospasm (moderate or severe) is occurring  
1147 before day 8, this measurement will replace the assessment at day 8±1.

1148 A supporting Ordinal logistic regression model (utilising all classified categories) will also be  
1149 used to provide odds ratio estimates (+/-95% confidence intervals) for the treatment effect  
1150 and associated significance levels (p-values).

1151 Secondary endpoints include the:

1152 -Incidence of new cerebral infarcts on CT scan at day 14±1, or before patient discharge,  
1153 (compared post-treatment CT scan).

1154 Exploratory endpoints include the:

1155 -Incidence of morbidity/mortality (DIND; death due to vasospasm, DIND, infarcts or  
1156 complications due to anti-vasospasm therapy) by patient discharge.

1157 -Need of anti-vasospasm rescue therapy by patient discharge.

1158 -Clinical outcomes at week 12 and week 52, following assessment with modified Rankin  
1159 Scale (mRS) scored 0-6 (with incidence of 'Good' outcome scores 0-2) and Glasgow  
1160 Outcome Scale (extended) (GOSE) scored 0-8 (with incidence of 'Favourable' outcome  
1161 scores 6-8), together with the Montreal Cognitive Assessment Tool (MOCA) (score 0-30  
1162 higher better) and Health related quality of life, assessed using the EQ-5D-5L and SF36. The  
1163 Length of stay in hospital and the ICU will also be assessed as measures of clinical outcome .  
1164

1165 The additional information reported as an addendum to the final report will specifically  
1166 include the final assessment for clinical outcome (mRS and GOSE), assessed at week 52,  
1167 together with any additional adverse events (specifically those that are CNS related), together  
1168 with the MOCA, EQ-5D-5L and SF36.

1169 These data can be considered binary, ordered categorical or interval in nature.

1170 All binary outcomes will be evaluated using the same methods as those for the primary  
1171 endpoint (Fishers exact test).

1172 Ordered categorical data will be analysed using the Cochran-Mantel-Haenzel (CMH) test  
1173 (with modified ridits). Ordinal logistic regression may be supplemented if other covariates of  
1174 interest are identified (e.g. age, gender, WFNS).

1175 Normally distributed Interval data will be analysed using an analysis of variance (ANOVA)  
1176 model including treatment group as fixed effect and (if possible) baseline or other  
1177 explanatory variables as covariates (e.g. age, gender, WFNS). Estimates of treatment effects  
1178 and treatment differences will use LS means and 95% confidence intervals.

1179 Non-parametric alternatives, however, will be substituted if these data are non-normally  
1180 distributed (eg: Length of stay). This may take the form of the Wilcoxon rank sum test or a  
1181 ranked based ANOVA model.

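### The only between-arm interval named for the primary endpoint is a Wald odds-ratio interval, and it does not exist if no implant patient has moderate or severe vasospasm

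*Protocol*

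**What the plan says.** All places are in the Protocol.

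- **Section 11, Power & Sample size.** The trial has 20 patients per arm: "A total of 40 patients (20 in each group) is in fact sufficient to detect a clinically relevant" difference. The planning rates are 20% on active and 70% on control, "70%) with a two tailed significance level of 5% and 84% power". The earlier implant trial is cited for more extreme rates: "investigations (Active: 7%, Control: 73"%).
- **Section 11, Efficacy Endpoints.** The primary comparison is a Fisher test: "Implant and Control groups will be investigated using Fishers Exact test. Proportions in the" "two groups with 95% Clopper-Pearson confidence intervals will be used to quantify the" size of the difference. A supporting ordinal logistic model over all graded categories is "used to provide odds ratio estimates (+/-95% confidence intervals) for the treatment effect", with p-values.
- **Section 11, Data Descriptions.** The interval type for those odds ratios is fixed here: "confidence intervals) and frequencies (if appropriate) and as odds ratios (with 95% Wald" intervals. The sentence goes on to limit this to cases where logistic regression is used.
- **Section 11, Efficacy Endpoints, later text.** All other binary outcomes follow the primary endpoint's method, that is, Fisher. Ordered outcomes get a CMH test, and ordinal logistic regression is optional.
- **Section 8, centralised neuroradiologist assessment, item 6.** The qualitative vasospasm grade has three classes: none/mild (one class), moderate and severe.

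No risk-difference interval, exact odds-ratio interval or fallback for a non-estimable model is named.

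**The concern.** Two separate intervals, one per arm, do not give an interval for the difference or ratio between arms, although the protocol assigns them that task. Under Null Hypothesis in section 11 it also says that p-values will, where possible, be accompanied by estimates of the treatment difference with 95% intervals. For the primary endpoint only the ordinal model's odds ratio meets that aim, and its interval is fixed as Wald.

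A Wald interval needs a finite estimate and a finite standard error. With 20 patients per arm and an implant expected to abolish most events, 0/20 on active is a realistic result. It is also the result most favourable to the implant. The report would then show a very small Fisher p-value with no interval on the effect, and the team would have to choose a substitute interval after seeing the data.

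**Working it through.** **1. The plan's own figure.** All 21 × 21 = 441 possible tables were enumerated for 20 per arm under independent binomials with rates 0.20 and 0.70, rejecting when the two-sided Fisher p is at most 0.05. Exact power is 84.6%, against the stated 84%. The figure reproduces. It rests on Fisher and does not involve the Wald interval.

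**2. When the ordinal Wald interval fails.** Let Y be the grade (none/mild < moderate < severe) and x = 1 for active. The model is logit P(Y ≤ k) = θ_k − βx. If all 20 active patients are none/mild and at least one control is moderate or severe, the likelihood keeps rising as β → −∞. There is then no finite estimate and no interval estimate ± 1.96 × SE. The 2×2 version shows the same thing: SE = √(1/a + 1/b + 1/c + 1/d) has no value when a = 0. Merging none with mild matters here, because it leaves no order among the event-free patients from which to estimate β.

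**3. How often no active patient has an event.** P(0/20) = (1 − p)^20.

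| Active vs control rate | Source | P(0/20 on active) | Any empty cell in the 2×2 table |
|---|---|---|---|
| 20% vs 70% | planning rates | 0.80^20 = 1.15% | 1.2% |
| 7% vs 73% | cited earlier trial | 0.93^20 = 23.4% | 23.6% |

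The small excess in the last column comes almost entirely from controls who all have an event: 0.70^20 = 0.08% and 0.73^20 = 0.18%.

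**4. Check on the planned model.** In 1,500 simulated trials per scenario the proportional-odds model was fitted to the three classes. The share of moderate-or-severe cases that are severe is not in the protocol, so 30% and 50% were assumed. No finite estimate was found in about 1% of trials at 20%/70%, and in 21% to 24% at 7%/73%. This agrees with step 3.

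**5. What those trials look like.** They are nearly always clear positives: 0/20 vs 6/20 already gives Fisher p = 0.020, and 0/20 vs 15/20 gives p = 7.7 × 10⁻⁷. Of the 441 tables, 80 have an empty cell, and 62 of those 80 are Fisher-significant.

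**6. An interval that survives.** The exact conditional odds-ratio interval exists in the same tables:

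- 0/20 vs 15/20: odds ratio 0, 95% interval 0 to 0.108.
- 0/20 vs 6/20: odds ratio 0, 95% interval 0 to 0.72.

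**The case against.** The strongest defence is that little depends on this interval. The Wald odds ratio belongs to one supporting model. The primary analysis, Fisher with a Clopper-Pearson interval per arm, stays defined with an empty cell. At the rates on which the sponsor planned, failure has about a 1% chance, and the 23% needs the more extreme cited rates, which the sponsor chose not to plan on. A missing limit would be visible to any reader. Estimates and intervals are promised only where possible, and a fallback for a model that does not converge is ordinary SAP content.

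Most of this stands and it sets the severity. It does not remove the point. The protocol itself names Wald, and itself says that per-arm intervals will quantify the difference. Those are statements in the document, not details left open.

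Two stronger readings are tempting and are not supported:

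- **That low-rate binary endpoints suffer even more.** The protocol sends all other binary outcomes to Fisher, and no binary logistic model is planned. The Wald rule applies only where a logistic model is used.
- **That Wald is at fault for contradicting Fisher, and profile likelihood would cure it.** In 2×2 tables, Wald excludes 1 with Fisher p > 0.05 in 16 of 441 tables (5.5% of trials at 20%/70%). Profile likelihood does so in 32 (6.2%). Those 2×2 Wald intervals are also not planned. The ordinal model tests a different hypothesis from Fisher on the dichotomy, so some disagreement is expected.

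**Conclusion.** The point holds as a minor reporting defect. The only between-arm interval named for the primary endpoint has about a 23% chance of not existing at the protocol's cited rates and about 1% at its planning rates. When it fails, the trial is almost always a clear success by Fisher.

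This rests on three assumptions:

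- The ordinal model uses the three-class qualitative grade. The protocol says only that all classified categories are used. If none and mild were graded apart, zero events on active would not by itself prevent a finite estimate.
- The cited and planned rates apply to being moderate or severe on that grade. The primary definition counts a single segment narrowed by a third or more, whereas the grade leaves one moderately narrowed segment in none/mild. An event-free active arm on the grade may therefore be somewhat more likely than shown.
- All 20 patients per arm have an assessable angiogram.

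The primary test, type I error, sample size and 84% power are not affected.

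**What to change.** 1. In Efficacy Endpoints, name one between-arm exact interval to stand beside the Fisher test for the primary and the other binary endpoints: either the exact conditional odds-ratio interval or an exact risk-difference interval. Keep the per-arm Clopper-Pearson intervals as descriptions of each arm, and stop describing them as quantifying the difference.
2. In Data Descriptions, replace the Wald interval for logistic-model odds ratios by profile likelihood, with a Firth penalised fit when the arms separate. State which vasospasm classes enter the ordinal model.
3. Carry the same wording into the SAP before unblinding, so that the interval is not chosen after the result is known.

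The cost is a few phrases and a software option, with no change to sample size or to the primary test. There is a small downside: exact intervals are somewhat wider, and the ordinal model may still differ from Fisher.
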